#### Step 3 active dissemination: parent information support group intervention

The data from the three-month follow-up assessment for Step 2 will constitute the baseline (or pre-group) data for Step 3. Participants in Step 3 will also complete an additional questionnaire at the first group session regarding their expectations of the group and what mental health support they might already be receiving. Medical records for the child of parents in Step 3 will be reviewed to record any hospital-based nursing or allied health staff involvement with the family.

On completion of the Information Support group, participants will be provided with the follow up questionnaire as part of the last group session. Follow up assessment of the group intervention will occur between April – September 2014. Participants in the waitlist control group will be completing the 6-month follow up assessment from baseline in Step 2 of the study at this time. This will provide the control comparison data to assess the additional impact of the group intervention, compared to receiving the booklet alone. The waitlist control group will then proceed to participate in the group intervention. All participants in Step 3 will be scheduled to complete a final follow up (single-group) assessment six months after they attended the group. This will provide repeated measures pre-post data regarding the longer-term efficacy of the group intervention. Participants will receive a prompt letter regarding six month follow up and approximately two weeks later a phone call, giving them the option to complete the questionnaire over the phone, online or receive a hard copy in the mail. Six-month follow up of participants in Step 3 is anticipated to occur between October 2014 – March 2015.

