**Methods/Design:**

The study will be conducted in an Australian regional paediatric hospital and will use a stepped care intervention that increases in intensity according to parental distress. All parents of children discharged from the hospital will receive a family resilience and wellbeing factsheet (Step 1). Parents of children attending selected outpatient clinics will receive a family resilience and wellbeing activity booklet (Step 2). Parents who receive the booklet and report psychological distress at three-month follow-up will be randomised to participate in a family resilience information support group or waitlist control (Step 3). The Step 3 control group will provide data to compare the relative effectiveness of the booklet intervention alone versus the booklet combined with the group intervention for distressed parents. These participants will then receive the information support group intervention. All parents in Step 2 and 3 will complete baseline, post-intervention and six month follow up assessments. The primary outcomes of the study will be changes in scores between baseline and follow-up assessments on measures of constructs of family resilience, including parental wellbeing, family functioning, family beliefs and perceived social support. Qualitative feedback regarding the utility and acceptability of the different intervention components will also be collected.

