#### Step 3 active dissemination: parent information support group intervention

Participants who report psychological distress at the 3-month follow up of Step 2 will be considered eligible to participate in Step 3 of the intervention. Psychological distress will be defined according to cut off scores on the Kessler Psychological Distress Scale (K10) (Kessler et al. 2003). There is some evidence that support groups are of optimal benefit for this portion of the target population (Turner et al. 2001). All parents reporting a K10 score above 15 (Slade et al. 2011) will be eligible for the group. Eligible parents will be contacted by phone by a member of the CHiRP research team and invited to attend an Information Support Group. Participants who agree to attend the Information Support Group will be randomly allocated to the group or waitlist condition using standard statistical computer software. Researchers will not be blinded to group assignment. Participants will be notified by phone and letter of the date of group commencement.

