### Sample size

In Step 1, it is expected that the Fact Sheet will be provided to 1050 parents of children discharged from paediatric hospital services based on an estimate of inpatient numbers over a 12-month period in 2011. There will be no direct data collection from this group.

A sample size calculation was conducted to guide recruitment for Step 2, the booklet intervention. Using mean estimates based on normative scores (Andrews & Slade 2001; Kabacoff et al. 1990; Sherbourne & Stewart 1991; Sixbey 2008) and a hypothesised effect size of 0.2 as a result of receiving the family resilience and wellbeing booklet, a minimum sample of 98 participants at the three-month follow up assessment will have sufficient power (0.8) to detect a significant difference between mean scores (using alpha 0.05) in a one-sample comparison of baseline and three month follow-up data. A larger sample size will be recruited, however, to allow for attrition and sufficient numbers of participants eligible for Step 3.

In Step 3, the Parent Information Support Group intervention, using a randomised waitlist control design, the sample size will be divided randomly and equally between the group condition and the waitlist control condition. A sample size calculation used mean estimates based on a sample of Australian patients diagnosed with a mental disorder (Kohn et al. 2012) using the K10 and normative scores for the other outcome measures of interest. Effect sizes of 0.5 and 0.3 were hypothesised as a result of receiving the booklet intervention and participating in the information support group intervention or being in the control group, respectively. A sample size of approximately 120 (60 per group) participants at the three month follow up assessment will allow detection of a significant difference between mean scores using an alpha level of 0.05 in a two-sample comparison of the group condition and control condition on the outcome measures, with a power of at least 0.8.

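### The main Step 3 ANCOVA names only the three-month score as baseline; adding each outcome's pre-booklet score, already collected, is a free improvement whose gain depends on correlations not given

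*Protocol article*

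**What the plan says.** Under Participants and recruitment, entry to Step 3 depends on the three-month assessment: "Participants who report psychological distress at the 3-month follow up of Step 2 will be considered eligible to participate in Step 3". The threshold is explicit: "All parents reporting a K10 score above 15 (Slade et al. 2011) will be eligible for the group". No condition is placed on the score before the booklet.

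Under Data collection procedures for Step 3, the same assessment becomes the starting point of the comparison: "The data from the three-month follow-up assessment for Step 2 will constitute the baseline (or pre-group) data for Step 3". The waitlist's six-month Step 2 assessment supplies the control data, to "assess the additional impact of the group intervention, compared to receiving the booklet alone".

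Under Statistical analyses for Step 3, the main comparison is an analysis of covariance of change from baseline to post-intervention follow-up, about 60 parents per arm. Further analyses are to adjust for baseline characteristics. These are not listed, and the pre-booklet score is neither named nor excluded.

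Under Data collection procedures for Step 2, all participants complete the outcome measures before receiving the booklet. Under Participants and recruitment, the booklet is sent only once that questionnaire is returned. A pre-booklet assessment therefore exists for every parent who reaches Step 3.

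**The concern.** Each Step 3 parent has two assessments before randomisation: one before the booklet and one three months after it. The main model is described with the second only.

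That second K10 score also decides who enters. Among randomised parents it is cut off at 15 from below, so it varies less and explains less of the follow-up K10 than it would in all Step 2 parents. A single reading also mixes a parent's lasting level with fluctuation around it. A second reading taken three months earlier may help to separate the two.

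Only precision is at stake. With about 60 parents per arm, it makes sense to use prognostic information that has already been collected. The truncation is direct for K10. For family functioning, beliefs and social support it acts only through their correlation with K10, but the argument for a second pre-randomisation reading is the same.

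**Working it through.** **The plan's own figure.** The only stated figure bearing on precision is 60 per arm for power of at least 0.8 at alpha 0.05 (Sample size, Step 3). Reading the hypothesised 0.5 and 0.3 as a between-arm difference of 0.2 SD, n per arm = 2 × (1.960 + 0.842)² / 0.2² ≈ 393 two-sided, and 60 per arm gives power 0.19. Reading 0.5 itself as the difference gives 63 per arm, with power 0.78 at 60. Neither reading reproduces 60 exactly. This is a separate matter, noted only because the covariate below would not repair it.

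**Inputs.**
- From the article: 60 per arm; about 353 in Step 2; selection on the three-month K10.
- Assumed, because the article gives none: correlations between assessments, and normality. Write a for pre-booklet with three-month, b for pre-booklet with follow-up, and c for three-month with follow-up. Variances are set to 1.

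**Formulas.** Residual variance with the three-month score alone is 1 − c². Adding the pre-booklet score reduces it by the fraction (b − ac)² / [(1 − a²)(1 − c²)].

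**Equal correlations, a = b = c = r.** The fraction simplifies to r² / (1 + r)².
- r = 0.5: 0.750 to 0.667, a fall of 11%.
- r = 0.6: 0.640 to 0.550, a fall of 14%.
- r = 0.7: 0.510 to 0.424, a fall of 17%.

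**Pre-booklet to follow-up correlation 0.1 lower, a = c = r, b = r − 0.1.**
- r = 0.5: (0.40 − 0.25)² / 0.75² = 0.0225 / 0.5625 = 4.0%.
- r = 0.6: (0.50 − 0.36)² / 0.64² = 0.0196 / 0.4096 = 4.8%.
- r = 0.7: (0.60 − 0.49)² / 0.51² = 0.0121 / 0.2601 = 4.7%.

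**Pure autoregressive decay, a = c = r, b = r².** Then b − ac = 0 and the gain is 0% at every r.

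**Does the gain survive selection?** A simulation kept the top 120/353 = 34% on the three-month score. That share is an assumption: 120 counts parents randomised, and the share eligible could be larger. Equal correlations were used.
- r = 0.5: outcome variance in the selected group 0.823; residual variance 0.753 with the three-month score, 0.698 with the pre-booklet score alone, 0.670 with both. The fall from adding the second score is 1 − 0.670/0.753 = 11%.
- r = 0.7: outcome variance 0.648; residual variance 0.509, 0.461 and 0.423. The fall is 1 − 0.423/0.509 = 17%.

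The narrowing is visible at r = 0.5. The three-month score explains 1 − 0.753/0.823 = 8.5% of outcome variance in the selected group, against 0.5² = 25% without selection.

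**Bias.** In a simulation with the same selection, equal correlations of 0.6 and 60 per arm, the ANCOVA on the three-month score alone gave a mean estimate of 0.199 for a true difference of 0.2.

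**Size in power terms.** At r = 0.6, 60 per arm and a difference of 0.2, power goes from 0.277 to 0.315 with equal correlations and stays at 0.277 under autoregressive decay. At a difference of 0.5 it goes from 0.928 to 0.958, or stays at 0.928.

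**The case against.** The strongest objection is that nothing here is an error. The last score before randomisation is the natural baseline for an added-effect comparison, and the article labels it as pre-group. Covariate lists are commonly left to a full protocol or analysis plan, neither of which is shown, and the planned further adjustment leaves room for the pre-booklet score. The gain rests on unknown correlations and may be nil. All of this stands, which is why the point is offered as an improvement and not as a fault or an omission.

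A reader might go further in several ways that the documents do not support.

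- **That Step 3 overclaims**, because parents who are not distressed after the booklet are absent and the abstract says "The Step 3 control group will provide data to compare the relative effectiveness of the booklet intervention alone versus the booklet combined with the group". But the sentence just before defines who is randomised: "Parents who receive the booklet and report psychological distress at three-month follow-up will be randomised to participate in a family resilience information support group". The full comparison is to "compare the relative effectiveness of the booklet intervention alone versus the booklet combined with the group intervention for distressed parents", and the methods sections claim only the group's additional impact. No passage says Step 3 will estimate the booklet's effect from its start; Step 2 addresses that.
- **That the run-in biases the comparison.** Selection precedes randomisation and applies alike to both arms. Nor does the rule simply remove those who improved: it also leaves out the never distressed and admits the newly distressed.
- **That precision is certainly lost.** The gain is zero under autoregressive decay.
- **That the control arm is credited with a booklet effect of 0.3 after its own baseline.** The sentence beginning "Effect sizes of 0.5 and 0.3 were hypothesised as a result of receiving the booklet intervention and participating in the information support group intervention" gives no time origin for either effect size, so this cannot be settled from the text.
- **That newly distressed parents recover more on their own, so allocation should be stratified by pre-booklet K10.** No passage establishes the premise, and covariate adjustment needs no change to the allocation.

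**Conclusion.** Step 3 validly estimates the effect of adding the group, compared with waiting, in consenting parents with K10 above 15 three months after the booklet. Its baseline is sound. The surviving point is a free improvement: the main analysis is described with a single pre-randomisation score, narrowed for K10 by serving as the entry filter, while an earlier reading of every outcome is already held.

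Under assumed correlations of 0.5 to 0.7, the second covariate reduces residual variance by about 11–17% if all correlations are equal. That is equivalent to about 12–20% more parents (1/0.889 = 1.125; 1/0.830 = 1.205). The reduction is about 4–5% if the pre-booklet to follow-up correlation is 0.1 lower, and nil under autoregressive decay. Which case applies cannot be known from the article. The benefit is therefore possible and modest, and the downside is negligible.

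**What to change.** In the main Step 3 analysis of covariance, prespecify each outcome's pre-booklet (Step 2 baseline) score as a second covariate beside its three-month score. Keep the three-month score as the baseline; the pre-booklet score is an addition and not a replacement. If a fuller protocol or analysis plan already names it, nothing further is needed.

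The cost is one line of text and one residual degree of freedom: with 120 parents, 116 instead of 117 after the intercept, arm and covariates. No new data, recruitment or change to the allocation is required.

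As an editorial clarification only, the abstract's comparison sentence and the Step 3 hypothesis under Study aim and hypotheses could describe the population as parents reporting K10 above 15 three months after receiving the booklet.

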#### Step 2 targeted dissemination: booklet intervention

As per Figure 1, baseline data for Step 2 will be collected through the CHiRP Parent Outpatient Survey. This will be completed by all participants who participate in Step 2, prior to receiving the Booklet intervention. The questionnaire will take approximately 20 minutes to complete and a random identification code will be generated to maintain participant confidentiality. Participants will complete the questionnaire at home or while waiting for the clinic appointment, and it will be available to complete in hard copy or online. Baseline data collection for Step 2 will occur from September 2013 to March 2014.

Follow up data will be collected from all participants in Step 2 at three and six months after completing the baseline assessment and receiving the Booklet intervention. On both follow up occasions, to minimise attrition, participants will receive a prompt letter advising that follow up will occur. Participants will be contacted by phone approximately two weeks after receiving the prompt letter and be given the option to complete the questionnaire over the phone with a member of the CHiRP team, be sent the questionnaire to complete in hard copy (and return it with a reply paid envelope), or complete the questionnaire online. Data collection for the three-month follow up assessment of Step 2 will occur between January – June 2014. Data collection for the 6-month follow up assessment is anticipated to occur between April - September 2014.

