#### Other

A follow up parent survey will measure the impact of Step 2, the booklet intervention. The questionnaire will be administered at three and six months after baseline. It will include the outcome measures as well as questions about changes to the child’s diagnosis in the past three months, questions about the acceptability of the booklet and questions to illicit participant’s self-reported knowledge, understanding and confidence to implement strategies. A follow up parent survey will also be used to assess Step 3. The questionnaire will be administered immediately following the group intervention and then six months later. The questionnaire will include the outcome measures as well as questions regarding perceived utility and acceptability of the group content and format.

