#### Step 3 active dissemination: parent information support group intervention

The Parent Information Support Group is an education, support and skills development group program directed toward parents experiencing psychological distress. The group program content will be based on the “Strong Parents, Resilient Families” booklet and will provide the additional benefit of an opportunity for discussion and practice of the strategies within a facilitated, interactive peer-supported environment.

Parents managing childhood chronic illness have significant demands on their time and participation in face-to-face groups can be low and attrition rates high (Stewart et al. 2012). In light of this, the information support group will combine face-to-face delivery with interactive online delivery strategies. The intervention will be conducted over six weeks. In week one, participants will attend a full day session (4 hours + 1 hour lunch) during which they will have the opportunity to connect with other parents, share their experience and interact with the facilitators to engage with the material in the “Strong Parents, Resilient Families” booklet. This session will include up to 15 participants and will be run by two trained facilitators with a background in psychology or allied health. Over weeks two to five, material pertaining to family resilience strategies will be posted once a week onto an online forum by a research team member who will act as moderator of the site. Participants will be encouraged to read the material, engage in the activity with their family, and post their comments for group online discussion. In week six, a final session will provide an opportunity for parents to meet face-to-face to discuss their experiences, review their participation in the program and complete the evaluation. A facilitator manual detailing the content, structure and format of each session and online material will maximise standardised delivery of the intervention content. Collaboration with outpatient clinic staff (e.g. Clinical Nurse Consultants or Social Workers) and carer support services will allow for delivery of the program to occur with the support of existing service providers.

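### In the Step 3 randomised comparison the two arms' outcomes are collected by different routes, in different settings and on different time anchors, and only the group arm's stated route depends on attendance

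*Protocol article*

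**What the plan says.** All references are to the protocol article.

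- **Group arm.** Data collection procedures, Step 3: "On completion of the Information Support group, participants will be provided with the follow up questionnaire as part of the last group session". Intervention, Step 3, places this at the week-six face-to-face meeting, where parents "review their participation in the program and complete the evaluation". Measures, Other, agrees on the timing: "The questionnaire will be administered immediately following the group intervention and then six months later".
- **Waitlist arm.** Data collection procedures, Step 3: "Participants in the waitlist control group will be completing the 6-month follow up assessment from baseline in Step 2 of the study at this time". The section states that this supplies the control data for judging the added effect of the group. Under Data collection procedures, Step 2, that follow-up starts with a prompt letter and then a phone call, at which parents "be given the option to complete the questionnaire over the phone with a member of the CHiRP team", or choose a posted or online form.
- **Calendar.** "Follow up assessment of the group intervention will occur between April – September 2014", and the Step 2 section gives the same months for the six-month follow-up.
- **Shared baseline.** The three-month Step 2 assessment is the Step 3 baseline in both arms. Its K10 score (above 15) also determines eligibility.
- **Scope of the six-month follow-up.** Data collection procedures, Step 2: "Follow up data will be collected from all participants in Step 2 at three and six months". The Step 3 section names it as the comparison outcome for the waitlist arm only.

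**The concern.** This is the only randomised comparison in the programme, and the Discussion relies on it for a rigorous evaluation of the support group. Randomisation makes the arms comparable at entry. It does not protect against measuring them differently afterwards. Three features of measurement are tied to allocation.

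1. Group parents answer at a session run by facilitators with other parents present, while waitlist parents answer remotely. Because mode and setting coincide with allocation, no analysis can separate their effect from the effect of the group.
2. A group parent who has stopped attending is not reached by the stated route. A waitlist parent is contacted whether engaged or not.
3. One assessment is anchored to the end of a group, the other to six months from the Step 2 baseline. All parents were selected on a raised K10, so scores may fall with time in either arm, and unequal intervals could then produce a difference of their own.

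The outcomes are self-reported and allocation is open, so answers can respond to setting. None of this can be repaired once the data are in.

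**Working it through.** **Side by side (from the article).**

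| Feature | Group arm | Waitlist arm |
|---|---|---|
| Occasion | Last session, week 6 | Six months after Step 2 baseline |
| Setting and mode | Face-to-face session | Phone, post or online |
| Depends on attending? | Yes, by the only route stated | No |
| Time anchor | End of the group | Step 2 baseline |
| Calendar window | April to September 2014 | April to September 2014 |

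The letter, phone and online routes appear for Step 3 only at the later assessment, six months after the group.

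**Timing.** Step 3 baselines fall between January and June 2014. The waitlist outcome is nominally 6 − 3 = 3 months after that baseline. The article gives no interval from Step 3 baseline to group start.

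- Equal intervals are possible. Three months is about 13 weeks, so a six-week group starting about 13 − 6 = 7 weeks after baseline ends when the waitlist assessment falls due.
- Unequal intervals are also possible. For a January baseline the waitlist outcome falls in about April (3 months), while the group window allows April to September (about 3 to 8 months).
- Sessions take up to 15 parents, so 60 parents need at least 60 / 15 = 4 groups, and finishing dates depend on when groups are formed.

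**Missingness (illustration; the article gives no attrition rate for either arm).** Let p be the share of an arm not measured and g the amount, in SD, by which their outcomes would be worse than those of parents who are measured. The observed mean then looks better by p × g, and the bias in the comparison is p(group) × g(group) − p(waitlist) × g(waitlist).

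- No waitlist loss, p(group) 10% to 33%, g 0.25 to 0.75 SD: from 0.10 × 0.25 = 0.025 SD to 0.33 × 0.75 = 0.25 SD.
- Waitlist loss of 10% with the same g in both arms: from (0.10 − 0.10) × 0.25 = 0 to (0.33 − 0.10) × 0.75 = 0.17 SD.

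Baseline adjustment in the planned ANCOVA would remove whatever part of this the baseline score explains.

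**Effect on the test (illustration).** Take 60 per arm, no true effect, a two-sided 5% test (sidedness is not stated), and a shift of b SD from measurement alone. The standard error is √(1 − ρ²) × √(2/60), where ρ is the baseline–outcome correlation. The rejection probability is Φ(b/SE − 1.96) + Φ(−b/SE − 1.96).

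| b (SD) | ρ = 0 | ρ = 0.5 |
|---|---|---|
| 0.05 | 0.059 | 0.062 |
| 0.10 | 0.085 | 0.097 |
| 0.20 | 0.195 | 0.244 |

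For b = 0.10 and ρ = 0, SE = 0.183 and b/SE = 0.548, so the result is Φ(−1.41) + Φ(−2.51) = 0.079 + 0.006 = 0.085.

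**The case against.** The strongest reply is that only the difference in mode and setting is actually written down. Several parts of that reply stand.

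- **Timing.** A reader might infer that the arms are assessed at different times. The article does not show this. Both share a calendar window, and the waitlist assessment is described as happening when the group follow-up does. What stands is that the anchors differ and no common interval is fixed. Selection on K10 applies equally to both arms and biases the contrast only if intervals differ.
- **Missingness.** A reader might infer that non-attenders are lost in one arm only. No passage says they are dropped, waitlist parents can be lost too, and the six-month follow-up covers all Step 2 participants. Chasing absentees may also be detail left to a fuller protocol, and the flow diagram is not available here. However, the article does name a route for this outcome, and that route is the session. The intention-to-treat wording treats every randomised parent as having completed, which supplies no data for those who did not.
- **Direction.** Answering an unblinded team member by phone may also distort replies, so a net bias towards the group arm is plausible rather than established.
- **Size.** Assuming 25% to 40% loss and a 0.3 SD gap gives 0.075 to 0.12 SD, which might be read as 38% to 60% of the planned effect. That reading is not supported. It sets waitlist loss to zero, and it divides by 0.5 − 0.3 = 0.2, a difference the article never states. With n per arm = 2 × (1.96 + 0.84)² / d², an effect of 0.5 needs 63 and 0.2 needs 393, so the planned 60 roughly fits 0.5. Against 0.5 the same shift is 15% to 24%.

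**Conclusion.** The point holds as a design weakness with a real risk of bias. By design, mode and setting of outcome collection differ between the randomised arms, and the only stated route to the group arm's post-intervention outcome requires attendance at the last session. The article itself says participation in face-to-face groups can be low and attrition high. Unequal follow-up time is possible because the anchors differ, but it is not certain.

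The size of the bias cannot be determined from the article. The illustrations rest on assumed loss by arm, an assumed outcome gap and an assumed baseline–outcome correlation. They show only that modest shifts matter at 60 per arm. The documents do not establish that the group effect is biased, or by how much.

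**What to change.** 1. Define the Step 3 between-arm outcome as one common assessment of every randomised parent, whether or not they attended. Use the six-month follow-up already scheduled for all Step 2 participants.
2. Use the same prompt letter, phone call and choice of phone, post or online in both arms. Fix the same window in both arms, counted from the Step 3 baseline or from randomisation.
3. If a group finishes after that date, move the assessment of both arms in that batch together. As already planned, waitlist parents start their own group only after this assessment.
4. Keep the last-session questionnaire with its outcome measures. The survey described under Measures, Other, includes them, and the single-group analysis of baseline, post-intervention and six-month scores in about 120 parents needs them. Only its use as the group arm's side of the randomised comparison should stop.

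The cost is protocol wording and scheduling, using contact procedures already planned. The between-arm outcome may be read some weeks after the last session, so it is no longer an immediate post-group measure. Some group parents will complete the questionnaire twice, and moving a batch departs from the six-month schedule for those parents. A common procedure equalises the influence of open allocation on self-report but does not remove it. The change has to be made before Step 3 outcome collection begins.
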